**Figure 4 F4:**
[figure not shown]
PACS study outcome measures and analyses. AIS, arterial ischaemic stroke; AuSCR, Australian Clinical Stroke Registry; BASICS, Brain Attack and Stroke in Children Screen; ED, emergency department; EMS, emergency medical services; PACS, Paediatric Acute Code Stroke; ROC, receiver operating characteristic; tPa, tissue plasminogen activator.

Due to the hospital-based nature of the proposed intervention, when powering this study, we have taken appropriate care of the hierarchical nature of the data, where individual patients are clustered within the treating hospitals. It is therefore appropriate to anticipate the presence of a design effect (expressed through the value of the intraclass correlation coefficient), as would have to be done in the situation of cluster-randomised studies. In addition, different hospitals will be able to recruit different numbers of patients, thus there will be a variation of cluster sizes.

Nine hospitals are participating in the study. At the time of receiving grant funding in July 2020, seven hospitals had agreed to participate in the study. Based on this consideration, assuming the settings of alpha=0.05, the intraclass correlation coefficient of 0.05 (corresponding to a small-to-medium hospital-specific effect) and the coefficient of variation of hospital-based cluster sizes of 0.5 (medium-to-high level of variation) with at least seven hospitals, recruiting the 98 patients with radiologically confirmed diagnosis of stroke in the pre-PACS implementation phase and 98 patients in the post-PACS protocol implementation stage (on average 14 patients per hospital for both pre-implementation and post implementation stages), will yield 80% power to detect a change from 0.15 to 0.40 in proportion of children diagnosed within 4.5 hours of symptom onset.

In addition, this sample size will be sufficient for further validation and continuous updating of the BASICS tool in order to further improve its predictive capacity (as the total number of screened patients is expected to be at least three times the number of confirmed strokes).^30
31^

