#### Brain Attack and Stroke in Children Screen clinical decision support tool (PACS substudy)

The purpose of the Brain Attack and Stroke in Children Screen (BASICS) paediatric stroke recognition tool aims to increase diagnostic certainty for triage nurses and emergency physicians, using readily available demographics, process of care factors and neurological symptoms. The tool to be developed will provide the user with a probability of stroke versus mimic diagnosis and the probability of ischaemic versus HS to guide decisions about the need for Code Stroke activation and selection of CT- or MRI-based imaging. In addition to determining the probability of stroke, BASICS will allow the user to input the pedNIHSS variables to produce a stroke severity score which is essential for decisions about the use of reperfusion therapies.^28^ Unpublished pilot work using two retrospective patient cohorts suggests the tool has an overall accuracy of 84% for correct differentiation of childhood AIS from mimics and 89% for HS from mimics. A paper-based version of the BASICS decision support tool will be piloted at three hospitals (RCH, MCH and QCH). On completion of the PACS study, development of an app-based version is planned and functionality will need to be tested in a further prospective dataset (figure 2).

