## Sample size and power calculations

We anticipate 326 patients with suspected stroke will be recruited during the protocol development and prospective phases of the study (based on numbers of patients recruited to institutional stroke registries in Victoria and New South Wales). Recent literature suggests that approximately one in three children with stroke symptoms will have a final diagnosis of stroke following imaging.^31
43–45^ Therefore, we anticipate 98 participants with a radiologically confirmed diagnosis of stroke in each study phase. Estimates of pre-implementation time to stroke diagnosis are based on extrapolation of local published data^13^ and audit data provided by three study sites. Estimates of post implementation time to stroke diagnosis are based on audit data from Queensland Children’s Hospital, where the proportion of children diagnosed within 4.5 hours increased from 15% to 40% during the 12-month period following introduction of their institutional PACS in 2019. We estimate that 15% of children will be diagnosed within 4.5 hours in the pre-implementation phase, increasing to 40% in the post implementation phase.

The *primary outcome* is the change in the proportion of children with stroke diagnosed within a 4.5-hour time window for reperfusion therapies, pre- and post-PACS implementation (figure 4). Time to diagnosis will be based on radiological confirmation of ischaemic infarction or haemorrhage on CT or MRI. This will be determined by calculating the time elapsed from last seen well to completion of neuroimaging, which is electronically recorded on imaging studies.

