Performance accuracy of the BASICS tools will be evaluated (patients dichotomised to diagnosis of stroke or mimic) by ORs, positive/negative likelihood ratios and receiver operating characteristic curves.Interobserver reliability of the BASICS tools will be evaluated using kappa score and confirmed by intraclass correlation coefficient and Lin’s concordance coefficient.Benchmarking primary and secondary outcomes (1) and (2) against adult best practice care through data linkage to the Australian Clinical Stroke Registry (AuSCR)^46^ and ambulance services data. Descriptive statistics will be used to summarise characteristics of children treated in paediatric versus adult hospitals, with differences tested using χ^2^ tests for categorical variables and rank-sum test for non-parametric continuous variables.

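### The same PACS children are to validate BASICS and continuously update it, and accuracy is tied to no version, so the reported figures may be optimistic or may mix versions

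*Protocol article*

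**What the plan says.** Four statements in the protocol article bear on this point.

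- **Sample size and power calculations (closing paragraph):** "this sample size will be sufficient for further validation and continuous updating of the BASICS tool in order to further improve its predictive capacity". The reason given is the ratio of screened to confirmed cases: "as the total number of screened patients is expected to be at least three times the number of confirmed strokes".
- **Sample size and power calculations (opening):** "We anticipate 326 patients with suspected stroke will be recruited during the protocol development and prospective phases of the study", and "we anticipate 98 participants with a radiologically confirmed diagnosis of stroke in each study phase".
- **Data analysis plan, Outcomes:** "Performance accuracy of the BASICS tools will be evaluated (patients dichotomised to diagnosis of stroke or mimic) by ORs, positive/negative likelihood ratios", together with ROC curves. No version of the tool is named.
- **Interventions, BASICS substudy:** "The tool to be developed will provide the user with a probability of stroke versus mimic diagnosis". The same section reports unpublished pilot accuracies of 84% (ischaemic stroke against mimics) and 89% (haemorrhagic stroke against mimics) from two retrospective cohorts. It places a paper version at three hospitals. It also says of an app planned for after PACS that its "functionality will need to be tested in a further prospective dataset".

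**The concern.** Validation asks how a fixed tool performs in children who had no part in shaping it. Updating uses children's outcomes to change the tool. Giving both jobs to one sample creates two separate risks.

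1. **Optimism.** If a child's data help to set the weights or the cut-off, and that child is then scored with the result, the accuracy obtained is apparent accuracy and tends to be too high.
2. **Mixed versions.** If the tool changes as the study runs and each child keeps the score from the version of the day, pooled likelihood ratios and ROC curves average over several tools and need not describe the one that clinicians will use.

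BASICS is intended to inform Code Stroke activation and the choice between CT and MRI. The only earlier evidence that the article reports is unpublished and retrospective, so the PACS figures would be the first prospective evidence described. A negative likelihood ratio that looks too good would make missed strokes appear rarer than they are.

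**Working it through.** **1. What the sample size was calculated for.** Inputs from the sample size section: 0.15 versus 0.40, 98 strokes per phase, 7 hospitals, mean cluster size 14, ICC 0.05, coefficient of variation 0.5, alpha 0.05 (two-sided assumed).

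- Design effect = 1 + ((1 + 0.5²) × 14 − 1) × 0.05 = 1 + 16.5 × 0.05 = 1.825.
- Standard error = √[(0.15 × 0.85 + 0.40 × 0.60) × 1.825 / 98] = √(0.3675 × 1.825 / 98) ≈ 0.083.
- Noncentral t with 2 × 7 − 2 = 12 degrees of freedom and noncentrality 0.25 / 0.083 ≈ 3.0 gives power 79.2%.

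The stated 80% is reproduced. It concerns time to diagnosis and says nothing about BASICS.

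**2. The reason given for BASICS.** 326 / 98 = 3.33, which agrees with a ratio of at least three. It implies 326 − 98 = 228 mimics. The ratio describes case mix. It does not show that one sample can both update and validate a tool. The pre-implementation phase identifies confirmed strokes only, so stroke-versus-mimic accuracy must come from the 326.

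**3. Optimism if updated children are scored by the updated version.** The article gives no number of predictors, updating method or true AUC, so these are assumptions. A logistic model was fitted to 98 strokes and 228 mimics, with independent normal predictors of which at most five carry signal. It was scored on the same children and on 20,000 new ones (200 replications). Optimism is AUC in the same children minus AUC in new children.

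| Predictors refitted | Optimism, attainable AUC 0.80 | Optimism, attainable AUC 0.88 |
|---|---|---|
| 2 | 0.000 | 0.004 |
| 10 | 0.027 | 0.018 |
| 20 | 0.062 | 0.040 |
| 30 | 0.083 | 0.064 |

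The two-predictor row stands in for light recalibration. With 20 predictors, attainable AUC 0.80 and a cut-off at predicted probability 0.3, the median positive likelihood ratio is 2.97 in the same children and 2.38 in new ones. The negative likelihood ratio is 0.32 against 0.45.

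**4. Fewer children.** If the three pilot hospitals supplied half the sample (163 children, 49 strokes; the share is assumed), optimism would be 0.04-0.06 with 10 predictors and 0.09-0.11 with 20.

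**5. Scoring before updating.** Assumptions: attainable AUC 0.85, a starting model from 200 children (60 strokes), updates after every 50 children, 150 replications.

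| Quantity (AUC) | 10 predictors | 20 predictors |
|---|---|---|
| Starting version, new children | 0.830 | 0.812 |
| PACS, each child scored before the update, pooled | 0.834 | 0.825 |
| Final version, new children | 0.841 | 0.835 |
| Final version re-scored on PACS children | 0.855 | 0.867 |

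Scoring first removes the optimism, but the pooled AUC lies between those of the starting and final versions. Re-scoring with the final version brings optimism back: 0.855 − 0.841 = 0.014 with 10 predictors and 0.867 − 0.835 = 0.032 with 20.

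**The case against.** A reader might infer that the reported accuracy is bound to be optimistic and can belong to no version of the tool. The documents do not support that. Nowhere does the article say that children used for an update are re-scored by the updated version, or that results are pooled across updates. The sentence on updating is a remark about sample size, not an analysis procedure. Step 5 shows no optimism when scoring precedes updating, and step 3 shows about none when only two coefficients are re-estimated. A tool also existed before PACS, because the retrospective cohorts produced accuracies for it. PACS could therefore be a genuine test of a fixed version.

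It can also be said that version control and optimism correction belong in an analysis plan that is not shown, and that BASICS is a piloted substudy with a secondary outcome. Both are fair. The absence of a correction method is not the finding.

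What remains is what the article does state: the same sample is declared sufficient for validation and for continuous updating, on a ratio that does not bear on the question. Recalibration alone is not an obvious reading either. Adjusting the intercept and a positive slope leaves the ROC curve unchanged, whereas the stated aim is better prediction and the Outcomes section lists no calibration measure. The later prospective dataset concerns the app's functionality. It is a partial safeguard for the app, but it does not protect the accuracy that PACS itself will report.

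**Conclusion.** The point holds as a risk built into the stated dual use, not as a demonstrated bias. BASICS accuracy from PACS may be optimistic or may mix versions, depending on an order of scoring and updating that the article leaves open. With all 326 children, AUC optimism ranges from about 0.00 to about 0.08 across 2 to 30 refitted predictors. It is larger with fewer children. These sizes rest on assumed predictor counts, attainable AUCs of 0.80 to 0.88 and a full refit of the coefficients. The primary outcome is unaffected. The matter deserves correction because the tool is meant to guide decisions and the remedy is cheap.

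**What to change.** In the closing paragraph of Sample size and power calculations, and in the BASICS item under Outcomes:

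- Lock one version of BASICS, both coefficients and cut-off, before its evaluation. Report odds ratios, likelihood ratios and ROC curves as validation for that version only.
- Remove continuous updating from the validation claim. Do any updating once, after data collection ends, and label it development.
- Report the updated version only with bootstrap optimism correction or leave-one-hospital-out performance.
- If the tool has already been changed during the study, use for each child only the score from a version fixed before that child's diagnosis was known, and report by version.

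This needs no extra patients, only changed wording and a modest amount of analysis. The price is that reported accuracy may be slightly less favourable and improvements to the tool wait until the end of the study. Data collection runs to mid-2026, so the change is best made before then.

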## Data analysis plan

### Outcomes

The *primary outcome* is the change in the proportion of children with stroke diagnosed within a 4.5-hour time window for reperfusion therapies, pre- and post-PACS implementation. This will be estimated using a mixed-effect logistic regression model with the dichotomous variable ‘diagnosed within 4.5-hour time window (yes/no)’ as the dependent variable, implementation phase as an independent fixed effect and hospitals as random effects.

*Secondary outcomes* (figure 4) include:

The proportion of children receiving reperfusion therapies will be analysed as for the primary outcome.Accuracy of emergency medical services (EMS) call taker, paramedic and ED physician stroke diagnosis against the gold standard diagnosis of radiologically confirmed stroke. Change in correctness of stroke (vs mimic) diagnosis, pre-implementation and post implementation of PACS will be estimated using a random-effect logistic regression model with dichotomised correctness of diagnosis as the dependent variable, intervention phase as an independent variable and hospital as a random effect.The impact of EMS call taker, paramedic and ED physician actions (eg, lights/sirens response and prenotification, PACS activation, MRI selection as the first imaging study in suspected AIS) on time to diagnosis will be analysed. Differences in times will be analysed using clustered quartile regression, with hospitals as clusters.The economic impact of shorter time to diagnosis, increased utilisation of MRI imaging and increased rates of reperfusion therapy in stroke patients will be measured using the CHU-9D, and hospitals linked services health utilisation and cost data.

Markov cohort model will be developed to quantify per-capita, national healthcare and societal costs economic costs, and the associated lifetime loss of QALYs and life years.

Performance accuracy of the BASICS tools will be evaluated (patients dichotomised to diagnosis of stroke or mimic) by ORs, positive/negative likelihood ratios and receiver operating characteristic curves.Interobserver reliability of the BASICS tools will be evaluated using kappa score and confirmed by intraclass correlation coefficient and Lin’s concordance coefficient.Benchmarking primary and secondary outcomes (1) and (2) against adult best practice care through data linkage to the Australian Clinical Stroke Registry (AuSCR)^46^ and ambulance services data. Descriptive statistics will be used to summarise characteristics of children treated in paediatric versus adult hospitals, with differences tested using χ^2^ tests for categorical variables and rank-sum test for non-parametric continuous variables.

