## Methods and analysis

### Study design

A quasi-experimental, two-tiered preintervention and postintervention study design will be used to evaluate the effects of the study interventions in tertiary children’s hospitals in Australia and New Zealand. The pre-implementation phase is the 3-year period from 2015 until 2017, reflecting the era prior to the launch of the Australian guideline for the acute management and diagnosis of stroke in children.^28^ The combined protocol development and post implementation phases are from 2018 to 2026. The study will follow the Transparent Reporting of Evaluations with Non-randomised Design statement for quasi-experimental non-randomised trials.^32^

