### Study participants, inclusion and exclusion criteria

During the pre-implementation phase, from 2015 to 2017, children aged 1 month to 18 years with radiologically confirmed stroke will be retrospectively identified from ICD10 principal diagnosis codes for stroke and then medical record review.

During the Code Stroke protocol development and post implementation phases from 2018 to 2026, children aged 1 month to less than 18 years of age with symptoms of less than 24 hours duration that are suspicious for stroke (also referred to as brain attacks)^34^ will be eligible for recruitment to the PACS study. Symptoms include altered consciousness; focal face arm or leg weakness; dysarthria; dysphagia; sensory disturbance; visual disturbance; limb incoordination/ataxia; visual/sensory neglect; pupillary abnormality; severe headache with associated focal neurology and seizure(s) with associated focal neurology^28^ (figure 1). Patients will be categorised into two final diagnostic groups: stroke or mimics, based on presence or absence of acute ischaemic or haemorrhagic infarction on brain imaging. Stroke will be further sub-categorised into AIS or haemorrhagic stroke (HS) as adjudicated by a paediatric radiologist. Children with acute neurological symptoms that are not relevant for stroke will be excluded from the study.

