## Data collection

### Pre-implementation and pre-protocol development phase

All sites will retrospectively collect data for confirmed strokes by case record review from 2015 to 2017, using the ICD-10 codes: I61.0–I61.6, I61.8, I61.9, I62.9, I63.0–I63.6, I63.8, I63.9, I64.0 and G45, for the primary aim of determining time to diagnosis prior to implementation of Code Stroke protocols across study sites (table 1).^40
41^

**Table 1 T1:** Data to be collected

Variables	Pre-implementation (2015–2017) confirmed stroke	Post implementation phase (2018 onwards) stroke	Post implementation phase (2018 onwards) mimics
Demographics	✓	✓	✓
Prehospital care*	✓	✓	✓
Presenting clinical features	✓	✓	✓
pedNIHSS (baseline, 24 and 48 hours)	✓†	✓	✓‡
EMS call taker and paramedic coded diagnoses*	✓	✓	✓
Sensitivity of ED physician diagnosis		✓	✓
Time to diagnosis§	✓	✓	✓
Timelines of care (pre- and post-arrival)	✓	✓	✓
Length of stay, acute hospital and inpatient rehabilitation	✓	✓	✓¶
Follow-up phone call following ED discharge for mimics to confirm no change in diagnosis		✓	✓
Rates of reperfusion therapy use (t-PA and ECR)	✓	✓	
Reperfusion therapy related serious adverse events	✓	✓	
Neurological outcomes: Outcomes: (PSOM and mRS) at discharge 7, 30 and 90 days. mRS at 30 and 90 days	✓	✓	
Child Health Utility (CHU-9D)		✓	
Costs of childhood stroke, using hospital/Medicare linked services health utilisation cost data		✓	

* For the subgroups of children transported to ED by ambulance.

† Paediatric version National Institutes of Health Stroke Scale (pedNIHSS) and Paediatric Stroke Outcome Measures (PSOM) may be derived retrospectively in some (but not all) patients from clinical assessment notes and should be collected if applicable.

‡ Only at baseline.

§ Time to diagnosis will be collected for all children presenting to the emergency department, regardless of mode of arrival and for inpatients where a Code Stroke is activated.

¶ Only if admitted.

ECR, endovascular clot retrieval; ED, emergency department; EMS, emergency medical services; mRS, modified Rankin score; tPA, tissue plasminogen activator.

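### The planned pre/post change in diagnostic correctness compares sensitivity in 2015–2017 with overall accuracy afterwards, and Table 1 lists no pre-phase diagnosis for ED physicians

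*Protocol article*

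**What the plan says.** The second secondary outcome (protocol article, Data analysis plan, Outcomes) is "Accuracy of emergency medical services (EMS) call taker, paramedic and ED physician stroke diagnosis against the gold standard diagnosis of radiologically confirmed stroke". The plan for change over time follows: "Change in correctness of stroke (vs mimic) diagnosis, pre-implementation and post implementation of PACS will be estimated using a random-effect logistic regression model". In that model the outcome is correctness as yes or no, phase is the explanatory variable, and hospital enters as a random effect.

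The phases and their populations are fixed elsewhere in the article:

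- Study design: "The pre-implementation phase is the 3-year period from 2015 until 2017".
- Study participants, inclusion and exclusion criteria, for the pre phase: "children aged 1 month to 18 years with radiologically confirmed stroke will be retrospectively identified from ICD10 principal diagnosis codes for stroke". For 2018 onwards, children with suspicious symptoms of under 24 hours' duration are eligible, and scans decide the final group: "Patients will be categorised into two final diagnostic groups: stroke or mimics, based on presence or absence of acute ischaemic or haemorrhagic infarction on brain" [scans].
- Pre-implementation and pre-protocol development phase: "All sites will retrospectively collect data for confirmed strokes by case record review from 2015 to 2017".
- Table 1, in that section, has a single pre-phase column, "Pre-implementation (2015–2017) confirmed stroke", and two columns for 2018 onwards, one for stroke and one for mimics. The row "Sensitivity of ED physician diagnosis" is blank in the pre-phase column and ticked in both later columns. The row for EMS call-taker and paramedic codes is ticked in all three, with a footnote limiting it to children who came by ambulance.

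**The concern.** A phase coefficient can be read as a change only if the outcome means the same thing in both phases. Here it does not. A mimic seen in 2015–2017 cannot enter the dataset, so the pre phase says nothing about specificity. From 2018 the same yes/no variable is dominated by mimics. The hospital random effect does not correct this, because the shift in case mix coincides with phase in every hospital.

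The model could therefore report better or worse recognition by call takers and paramedics when only the composition of the sample changed. The article's Discussion expects the work on decision tools to inform paramedic practice guidelines, so a misread result could carry weight. For ED physicians the article plans a pre/post change while its own data table lists no pre-phase value.

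**Working it through.** **The plan's own figures.** No effect size or power is stated for this outcome. The only power figure, 80%, belongs to the primary outcome and is not in dispute. What is needed from Sample size and power calculations is the expected case mix: 326 suspected strokes in the development and prospective phases, and 98 confirmed strokes per phase.

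**Case mix.**
- Pre phase: 98 strokes, 0 mimics.
- Later phase: 98 strokes and 326 − 98 = 228 mimics. Stroke share w = 98/326 = 0.30; mimic share 228/326 = 0.70.

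**What the model compares.** Let Se and Sp be a rater's sensitivity and specificity, the same in both phases.
- Pre: P(correct) = Se.
- Post: P(correct) = w × Se + (1 − w) × Sp.
- Difference with no true change: (1 − w) × (Sp − Se) = 0.70 × (Sp − Se).

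**Size.** The article gives neither Se nor Sp, so every pair below is an assumption.

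| Se | Sp | Pre | Post | Difference | Odds ratio |
|---|---|---|---|---|---|
| 0.50 | 0.80 | 0.50 | 0.30×0.50 + 0.70×0.80 = 0.71 | +0.21 | 2.4 |
| 0.80 | 0.50 | 0.80 | 0.30×0.80 + 0.70×0.50 = 0.59 | −0.21 | 0.36 |
| 0.40 | 0.95 | 0.40 | 0.785 | +0.385 | 5.47 |
| 0.80 | 0.85 | 0.80 | 0.835 | +0.035 | 1.26 |
| 0.70 | 0.70 | 0.70 | 0.70 | 0 | 1.00 |

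The odds ratio is post/(1 − post) divided by pre/(1 − pre); for the first row (0.71/0.29)/(0.50/0.50) = 2.4. Over Se 0.4–0.8 and Sp 0.5–0.95 it runs from 0.36 to 5.47.

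**Dependence on the stroke share.** The 30% covers all suspected strokes. EMS codes exist only for children who came by ambulance, and the stroke share among them is not given. With the article's rounder figure of one in three, the first row becomes 0.67 × 0.30 = 0.20. With an assumed share of one half it becomes 0.50 × 0.30 = 0.15. The size changes; the sign and the cause do not.

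**ED physicians.** Table 1 ticks this item only for 2018 onwards. On the data listed there, the 2015–2017 level of the phase variable is empty for this rater.

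**The case against.** **A narrower reading.** Correctness could be meant only for true strokes, that is, whether a stroke was called a stroke and not a mimic; Table 1 does name the ED item a sensitivity. The comparison would then be stroke against stroke. The text does not support this: the outcome is accuracy against a radiological gold standard, nothing restricts the model to confirmed strokes, and Table 1 ticks both diagnosis rows for mimics.

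**Another pre period.** The development period from 2018 includes mimics and might serve as the baseline. But Study design defines the pre phase as 2015–2017, and Table 1 labels 2018 onwards as post implementation.

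**An unseen analysis plan.** It may settle the matter. The article, however, already fixes outcome, model, covariate and raters, and these conflict with its own eligibility rules and data table. That is a contradiction, not an omitted detail.

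**What stands.** A reader might infer that ED-physician diagnoses from 2015–2017 do not exist. The documents show only that Table 1 lists none; the full variable list is in supplemental e-Table 2 and the outcome summary in figure 4, neither of which is shown. Even if such diagnoses were found, the lack of pre-phase mimics would remain.

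A reader might also infer that the model is bound to give a large and significant false effect. That depends on the unknown gap between sensitivity and specificity. At 98 versus 326 children, ignoring both clustering and the ambulance restriction, the chance of a significant result with no true change runs from 5% when the two are equal, through 13% at 80%/85%, to 99% at 50%/85%. Actual ambulance numbers will be smaller and are not stated.

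**Conclusion.** The point holds. As written, the pre/post change in stroke-versus-mimic correctness cannot be estimated, because the pre phase has no mimics by design. For call takers and paramedics the phase effect contains an artefact of about 0.70 × (specificity − sensitivity): 21 points in either direction for an assumed 30-point gap, near zero if the two are close. This rests on the planned 98/326 stroke share, which may not apply to children brought by ambulance. For ED physicians, no comparison with 2015–2017 is possible on the data listed in Table 1.

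It would go too far to say that secondary aim 3 as a whole would be answered wrongly. That aim concerns the utility of decision support tools, and the BASICS tool has its own stroke-versus-mimic evaluation by likelihood ratios and ROC curves, which needs no mimics from 2015–2017. Only the phase-change part of the accuracy outcome is affected. The primary outcome uses confirmed strokes in both phases and is untouched. The plan should be corrected before analysis, but this is not a threat to the main result.

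**What to change.** 1. Limit the 2015–2017 versus post model to children with confirmed stroke who came by ambulance and have an EMS call-taker or paramedic code, and label the estimate change in sensitivity.
2. State that the phases still differ in how cases are found: stroke ICD-10 codes in the pre phase, suspicious symptoms of under 24 hours from 2018. Apply the same symptom-duration restriction to both where duration is recorded.
3. Report specificity, overall accuracy and all ED-physician accuracy within the prospective cohort only, with sensitivity and specificity shown separately.
4. Limit any comparison there of before and after a site's go-live to those of the five hospitals without a protocol at commencement that have prospective data from before go-live. The four with existing protocols have no prospective period before theirs, and site approvals ran only from August 2021 to September 2023 (Study timeline, ethics approval and dissemination plan), so the period may be short or absent elsewhere too.

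Items 1 to 3 need changed wording and use data already planned; the symptom-duration restriction works only where the pre-phase records allow it. The price is that the change since 2015–2017 in overall correctness, and any such change for ED physicians, is dropped. The sensitivity comparison will rest on at most 98 strokes per phase, fewer after the ambulance restriction, and will be correspondingly imprecise.
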